#### Stage 2:

The primary outcome measure is overall survival (OS). Overall survival is calculated from the date of randomisation to death from any cause. Those patients still alive will be censored at the date last seen.

The secondary outcome measures are: Toxicity, quality of life, quality assurance and health economics.

- **Toxicity:** will be scored using the NCI CTCAE v3.0 and RTOG acute radiation morbidity scoring criteria at baseline, during treatment and at pre-specified time points on follow-up. Serious adverse events will be monitored “real-time” by the Chief Investigator and TMG.
- **Quality of Life (QoL):** will be documented through the use of EORTC-C30 plus oesophageal specific modules (OES18) and dermatology life quality index (DLQI) at baseline, during treatment and at pre-specified time points on follow-up.
- **Quality assurance (QA):** A detailed QA program will be in place to ensure adherence to the protocol (please see separate radiotherapy protocol). Major and minor deviations will be collected.

- **Health Economics (HE):** HE analysis will be performed using appropriate data collected on the CRFs, from relevant cost and resource utilisation data collected from finance and clinical staff, from administration of EQ-5D at baseline, during treatment and at pre-specified time points on follow-up.

NB: Although activity, safety and feasibility will not be formally assessed in the control arm in Stage 1, the randomisation of patients will continue using the same process and on a 1:1 allocation and therefore those patients in Stage 1 will be included in the analysis of Stage 2.

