#### **5.4 Follow up**

1. Patients will be seen 3-monthly for the first year, 4 monthly for the second year and yearly for a minimum of 5 years after treatment, after which follow up should be according to local guidelines.
2. Endoscopic assessment and/or CT scans to investigate symptoms suspicious of recurrence as clinically indicated. In the case of local recurrence it will be important to ascertain the relationship of the recurrent disease to the radiotherapy field by comparing endoscopic data at recurrence with the diagnostic/staging endoscopy/EUS and/or CT data with the staging/planning CT scans.
3. Quality of life QLQ-C30 + oesophageal module (QLQ-OES18) + dermatology life quality index (DLQI) (Annually).
4. State of Health (EQ-5D) and Healthcare Resource Utilisation Log (Annually).
- 5. Where recurrence is diagnosed by investigations including endoscopic assessment we request a biopsy sample for translational research.**

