### **10.3 Loss to follow-up**

If a patient is lost to follow-up the WCTU will request the centre contact the patient's GP to obtain information on the patient's status. If needed and the patient has given the necessary consent, they will be traced via the National Health Service Information Service (NHS IC) or the NHS Central Register.

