### 12.3 Sample size calculation

#### Stage 1:

The treatment failure-free rate in patients treated with CRT is approximately 60% at 24 weeks. With the addition of cetuximab it is felt that a treatment failure-free rate of less than 60% would not be sufficiently large enough to warrant further investigation in a Phase III setting, but that a rate of 75% or higher would warrant further investigation. Using a Fleming's single stage design,  $p_1=0.60$  and  $p_2=0.75$ , setting  $\alpha=0.05$  and 90% power 83 patients would be required. To allow for 10% not being assessable and with a 1:1 allocation 90 patients will be recruited into each arm, a total of 180 patients. The IDMC will review the treatment failure-free rate, along with toxicity and feasibility, before they endorse continuation into Stage 2.

#### Stage 2

Calculations were performed using the ART package in Stata 9 assuming a 3 year recruitment period followed by 1 year of follow up (based on a 2-sided log rank test). The 2 year overall survival rate in patients treated with CRT is approximately 35%. In order to detect an improvement in 2 year overall survival from 35% to 47.5% (Hazard Ratio [HR] =0.71) with 80% power at a 5% significance level a total of 420 patients (269 events) are required. A total of 210 patients will be recruited to each arm.

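### The overall survival rule stops living patients at the date last seen but sets no matching limit on deaths; read literally, this biases the survival curves downward and leaves the logrank comparison almost unchanged

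*Protocol*

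**What the plan says.** Protocol 12.2 (Stage 2) defines the outcome: "Overall survival is calculated from the date of randomisation to death from any cause". It then adds: "Those patients still alive will be censored at the date last seen". It gives no data cut-off date and no limit on how a death may become known.

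Three other sections bear on how this works in practice:

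- **5.4, visit spacing.** "Patients will be seen 3-monthly for the first year, 4 monthly for the second year and yearly for a minimum of 5 years after treatment".
- **10.3, patients lost to follow-up.** The trials unit asks the centre to obtain the patient's status from the GP. If needed, and if the patient has consented, "they will be traced via the National Health Service Information Service (NHS IC) or the NHS Central Register".
- **10.7, longer-term follow-up.** This may be carried out through the same national sources.

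The main analysis is a logrank test (12.5). Stage 2 is sized in 12.3 on 3 years of recruitment plus 1 year of follow-up, "with 80% power at a 5% significance level a total of 420 patients (269 events) are required".

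**The concern.** The two halves of the rule can use different information. A GP or register can report that a patient has died, and the death then enters the analysis at its date. The same source can report that a patient is alive, but that patient has not been seen, so on a literal reading the follow-up ends at the last visit. The time at which a patient leaves the risk set then depends on whether the patient is dead or alive. Kaplan-Meier estimation and the logrank test assume that it does not.

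The direction of the error follows directly. Survivors leave the risk set too early while deaths after their last visit still count, so each such death is divided by too few patients and the curve falls too fast. Gaps between visits are longest after month 24, so the error is largest there. At stake is mainly the level of the survival curves, including the survival data from which the QALYs in section 15 are derived. A loss of power is secondary.

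**Working it through.** **1. The protocol's own figure.** Inputs from 12.3 (Stage 2): 2-year survival 35% v 47.5%, two-sided 5%, 80% power, 210 patients per arm, 3 years of accrual plus 1 year.

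- Hazard ratio = ln(0.475)/ln(0.35) = 0.709.
- Events (Schoenfeld) = 4 × (1.960 + 0.842)² / (ln 0.709)² = 266. The Freedman formula gives 271.
- Yearly hazards = -ln(0.35)/2 = 0.525 and -ln(0.475)/2 = 0.372.
- Event probability with accrual A = 3 and follow-up F = 1 is 1 - [exp(-hF) - exp(-h(A+F))]/(hA), which gives 0.702 and 0.585.
- Expected events = 210 × (0.702 + 0.585) = 270.

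The stated 420 patients and 269 events reproduce, so the sample size is not in question.

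**2. The effect of the censoring rule.** The same design was simulated with exponential survival, uniform entry and analysis at year 4. Visits fell at about months 3, 6, 9, 12, 16, 20 and 24 and then yearly, timed from randomisation. There were 8,000 simulated trials, and nobody stopped attending.

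| Rule | Events | 2-year survival | Hazard ratio | Power |
|---|---|---|---|---|
| All followed to the cut-off | 270 | 35.0% / 47.4% | 0.7075 | 80.0% |
| All deaths counted, survivors stop at last visit | 270 | 33.7% / 46.2% | 0.7135 | 77.6% |
| As above, half of survivors updated to the cut-off | 270 | 34.4% / 46.8% | 0.7089 | 79.6% |
| Deaths and survivors both stop at last visit | 247 | 35.0% / 47.4% | 0.7076 | 76.4% |

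Type I error under the second rule is 4.9%. Repeat simulations of the first two rows put the power loss between 1.1 and 2.4 points.

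**3. Three-year survival.** The true values are 0.35^1.5 = 20.7% and 0.475^1.5 = 32.7%. Under the second rule the estimates average 16.4% and 27.3%, against 20.7% and 32.6% with full follow-up. The shortfalls are 4.3 and 5.3 points.

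**4. Size relative to the comparison.** The shift in the log hazard ratio is ln(0.7135/0.7075) = 0.008. The standard error with 269 events is about the square root of 4/269, or 0.12. The 2-year difference between arms is 12.4 points with full follow-up and 12.5 points under the second rule.

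**5. Longer follow-up.** With analysis at year 5 and full attendance, 2-year survival is 35.0% / 47.5% under either rule, because everyone has passed the month-24 visit. Power is 86.5% with full follow-up and 85.4% under the second rule.

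**6. If patients stop attending (assumption; the protocol gives no Stage 2 rate).** Suppose every death is still traced and no survivor is ever updated. At 5% per year, 2-year survival is 32.7% / 44.9% and power 76.0%. At 10% per year, it is 31.6% / 43.6% and power 74.2%.

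**The case against.** The asymmetry is inferred. The protocol does not say that deaths count whenever they are found, nor that a survivor confirmed alive is returned to the last visit. GP and register tracing yields status in both directions, and a sensible trials unit might take *seen* to include it. Unscheduled investigations for suspected recurrence (5.4) and the 18-month quality-of-life assessment (section 14) also create contacts that the simulation ignores. The simulated case is therefore a limit, and with half of survivors updated the power loss is only 0.4 points. This stands, and it is why the point rests on a literal reading.

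The 3-year estimate is not a design target. About 70 patients per arm could reach 3 years by the assumed analysis date, of whom 70 × 0.207 = 14 to 15 and 70 × 0.327 = 23 would still be at risk. That also stands, though the bias adds to the imprecision.

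An analysis plan could define the cut-off and the status check. It could not credit survivors known only through a GP or register without departing from the wording of 12.2, so the wording itself is a fair target.

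A reader might infer that the primary comparison is materially damaged. The documents do not support that: no events are lost, type I error is kept, and the hazard ratio moves by well under a tenth of its standard error. Nor do they support treating the larger losses in step 6 as expected, since those rest on an assumed rate of non-attendance.

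**Conclusion.** The point holds as a flaw in wording that, read literally, biases the survival curves. In the limiting case both arms are about 1.2 points too low at 2 years and 4 to 5 points too low at 3 years. The hazard ratio is about 0.714 instead of 0.707 and power is 1 to 2.5 points lower. These figures assume exponential survival at the protocol's design rates, full attendance, all deaths known, no survivor contact after the last scheduled visit, and analysis at 3 + 1 years. Any updating of survivors reduces the bias.

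**What to change.** In 12.2, censor living patients at the date last known to be alive from any source: clinic, GP or, where consented, register. State one data cut-off date that applies to deaths and survivors alike, and ask centres to update every patient's vital status to that date before the analysis. Updating survivors is preferable to discarding deaths after the last visit, which also removes the bias but leaves about 247 events and 76% power.

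The cost is a sentence or two in 12.2 and a little extra data chasing, with no added patients or procedures. Two limits apply. Register tracing is open only for patients who gave the separate consent described in 10.3 and 13.4. A status check of all patients also goes further than 10.3, which covers only those lost to follow-up.

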Assessing response to chemo-radiation, without surgically removing the oesophagus for histological examination, is notoriously difficult. Endoscopy negative rates following CRT range from 30-80% (mean 61%). Although not a reliable marker for pathological complete response (pCR) within the surgically resected specimen endoscopic response is strongly correlated with long-term survival. No other technique has been shown to be more reliable though trials are ongoing into the role of 18-FDG PET and EUS guided FNA in this setting. PET assesses metabolic activity as opposed to size as for CT. This means PET is able to determine benign from malignant lesions and is not only effective in detecting the primary tumour, but also is more sensitive in detecting small nodal and distant metastases. It is likely to become more commonly used after the results of larger trials and availability of equipment. It is not clear whether the presence of the EGF receptor predicts for response to cetuximab. Although not a pre-requisite for entry into this study, this and other predictors of response will be the subject of associated translational research.

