### 12.4 Interim monitoring and analyses

The first planned analysis of both trial arms will occur after a total of 60 patients have been recruited (30 patients in each arm). The research arm will be analysed to exclude any unexpected early toxicities, notably an excess of mucositis.

Interim analysis of the accumulating data will then be performed at regular intervals (annually) for review by the IDMC. These analyses will be performed by the WCTU. The IDMC will review the outcome Stage 1 is complete to endorse continuation into Stage 2.

The IDMC will review the results and, with consideration of any results from any relevant external trials, make a recommendation to the Trial Steering Committee (TSC) on whether the trial should continue recruitment or close to recruitment. While the trial is recruiting, only the appropriate staff at the WCTU and the IDMC will see the result of the interim analyses.

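### Stage 1 tests the research arm against a poorly sourced fixed 60% and excludes the 90 concurrent randomised controls from formal assessment

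*Protocol*

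**What the plan says.** Protocol section 12.2 defines the Stage 1 primary outcome as the treatment failure rate at 24 weeks in the research arm. Failure is residual disease at endoscopy and/or biopsy, and/or RECIST progression on CT. The note that closes section 12.2 says: "Although activity, safety and feasibility will not be formally assessed in the control arm in Stage 1". It adds that 1:1 randomisation continues and that Stage 1 patients enter the Stage 2 analysis.

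Section 12.3 gives the benchmark: "The treatment failure-free rate in patients treated with CRT is approximately 60% at 24 weeks", citing references 23-30. The test is set out as "Using a Fleming's single stage design", with 60% as the rate not worth pursuing, and "a rate of 75% or higher would warrant further investigation". At alpha 0.05 and "90% power 83 patients would be required"; 90 are recruited to each arm. The IDMC reviews this rate with toxicity and feasibility before endorsing Stage 2.

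Section 2.4 reports, from references 32-39, "Endoscopy negative rates following CRT range from 30-80% (mean 61" per cent).

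Section 12.4 describes a first look at 60 patients, 30 per arm. It introduces this as an analysis of both arms and then says: "The research arm will be analysed to exclude any unexpected early toxicities, notably an excess of mucositis".

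**The concern.** Section 2.5 states the first purpose as finding out whether adding cetuximab shows evidence of benefit. A single-arm test against a constant answers a different question: whether these centres, with this assessment schedule and cetuximab, do better than 60%. The two questions coincide only if chemoradiation alone would have given 60% in this trial.

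That is uncertain. The cited references do not report the figure. The nearest figure in the document measures something narrower than the trial endpoint, and it varies widely between series. Meanwhile 90 randomised controls have the same week-24 endoscopy, biopsy and CT (sections 5.3 and 5.5), so the trial itself will measure the number that the benchmark stands in for.

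The two possible errors differ in cost. A false no-go ends the trial with nothing to catch it. A false go commits a further 240 patients, although the randomised Stage 2 survival test still protects the final conclusion.

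**Working it through.** **Inputs.** From section 12.3: null rate 0.60, target 0.75, alpha 0.05, power 90%, 83 assessable patients, 90 recruited per arm. From section 2.4: endoscopy-negative mean 61%, range 30-80%.

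**The plan's own figure.** One-sample normal approximation with one-sided alpha:

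n = [(1.645 × √(0.60 × 0.40) + 1.282 × √(0.75 × 0.25)) / 0.15]² = 82.3, rounded up to 83.

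This reproduces the stated size. A two-sided 5% test would need 103, so the design is one-sided. The arithmetic is not at fault.

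**Cut-off.** The protocol states none. For n = 83, the smallest exact cut-off with P(X ≥ r | 0.60) ≤ 0.05 is r = 58 (69.9%). Its exact alpha is 0.041 and its power at 75% is 0.884.

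**Chance of passing.** P(X ≥ 58 | n = 83, p) depends only on the true research-arm rate p:

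| True research rate | 60% | 65% | 70% | 75% |
|---|---|---|---|---|
| P(go) | 4.1% | 20.8% | 56.3% | 88.4% |

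Read against the true control rate, this becomes:

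| True control rate | P(go), no effect | P(go), 15-point gain |
|---|---|---|
| 50% | <0.1% | 20.8% |
| 55% | 0.4% | 56.3% |
| 60% | 4.1% | 88.4% |
| 65% | 20.8% | 99.0% |
| 70% | 56.3% | >99.9% |

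The design's error rates hold only in the 60% row.

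**Source of the 60%.** In section 19, references 23-30 are a radiobiology text, two EGFR and radiation papers, a head-and-neck trial, a colorectal trial, two lung trials and one report of cetuximab with chemoradiation in oesophageal and gastric cancer. None addresses the failure-free rate after chemoradiation alone in oesophageal cancer. The endoscopy series are references 32-39. That the 61% lies behind the 60% is an inference; the document shows no other candidate.

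**Effect of the endpoint mismatch alone.** The documents do not say how many endoscopy-negative patients have CT progression, so I assume 5%, 10% or 15%. The comparable control rate is 61% × (1 − share), and a 15-point gain is added to it:

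| Assumed share | Control rate | P(go) with 15-point gain |
|---|---|---|
| 0% | 61% | 92% |
| 5% | 58% | 78% |
| 10% | 55% | 56% |
| 15% | 52% | 32% |

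This mismatch works only towards a false no-go.

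**What the controls can show.** With all 90 per arm at 60% and 75%, the 95% CI half-width for the difference is 1.96 × √(0.60 × 0.40/90 + 0.75 × 0.25/90) = 0.135, or 13.5 points. A formal one-sided 5% comparison with 83 per arm has 66% power and would need 166 per arm for 90%.

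**The case against.** The design is conventional, disclosed and correctly sized, and the passing rule is not mechanical. Sections 1.2, 12.3 and 12.4 describe an IDMC judgement on activity, toxicity, feasibility and external trials, and section 18 leaves the decision to the TSC. All of this stands, so the probabilities above describe the statistical criterion and not the final decision.

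A reader might infer that the controls are ignored altogether. The text does not go that far. Section 12.4 calls the 60-patient look an analysis of both arms, the IDMC sees accumulating data annually, nothing bars it from seeing control rates, and the Stage 1 controls count in Stage 2. What the protocol rules out is formal assessment. On mucositis, section 12.4 is ambiguous but not plainly wrong.

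A reader might also take the 30-80% range as licence to suppose controls at 75% or 80%, with a harmful drug passing easily. That range belongs to the endoscopy-only measure across published series. It is not a range for this trial's endpoint, and the CT component argues for a lower control rate. A false go is possible if controls exceed 60%, but the documents give less reason to expect it.

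The wrong reference numbers are probably clerical, since 23-30 and 32-39 are both runs of eight. That would confirm the endoscopy series as the basis without making their measure equivalent to the trial endpoint.

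**Conclusion.** The point holds as a weakness in how Stage 1 is specified. The activity criterion depends on a benchmark whose citations do not support it, and the protocol sets aside from formal assessment the concurrent controls that could check it. The size is material: a control rate 5 points below 60% cuts the chance of passing with the planned gain from 88% to 56%, and 10 points below cuts it to 21%; 5 points above raises the chance of passing with no effect from 4% to 21%. These figures assume 83 assessable patients and the derived cut-off of 58.

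It would be tempting to go further and also require the research-arm rate not to fall below the control rate. The numbers do not support that. With 83 per arm, such a hurdle leaves the false no-go case unchanged (50% against 65%: 20.8% before and after). For a true 5-point gain (70% against 75%) it lowers the chance of passing from 88% to 75%, and with equal arms at 75% from 88% to 53%. It would stop the trial on an unpowered point estimate. The control data should calibrate the benchmark and not serve as a second test.

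**What to change.** In the note at the end of section 12.2, replace the clause that excludes the controls with text such as:

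> The 24-week failure-free rate, toxicity and dose modifications will be analysed identically in both arms at Stage 1, and the IDMC will receive both rates and the difference with 95% CI alongside the Fleming result.

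Keep the rest of the note, keep the Fleming rule as the activity criterion, and add no further stopping hurdle. The IDMC could then see that the 60% does not fit this trial before it recommends stopping or continuing.

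In section 12.4, state that an excess of mucositis at the 60-patient look is judged against the 30 controls. In section 12.3, correct the references for the 60% and say whether the figure refers to endoscopy alone or to the section 12.2 endpoint.

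The cost is a small amount of extra tabulation for the IDMC. No additional patients, visits or investigations are needed, and section 12.4 already restricts interim results to appropriate trials unit staff and the IDMC while recruitment is open.

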### 12.3 Sample size calculation

#### Stage 1:

The treatment failure-free rate in patients treated with CRT is approximately 60% at 24 weeks. With the addition of cetuximab it is felt that a treatment failure-free rate of less than 60% would not be sufficiently large enough to warrant further investigation in a Phase III setting, but that a rate of 75% or higher would warrant further investigation. Using a Fleming's single stage design,  $p_1=0.60$  and  $p_2=0.75$ , setting  $\alpha=0.05$  and 90% power 83 patients would be required. To allow for 10% not being assessable and with a 1:1 allocation 90 patients will be recruited into each arm, a total of 180 patients. The IDMC will review the treatment failure-free rate, along with toxicity and feasibility, before they endorse continuation into Stage 2.

#### Stage 2

Calculations were performed using the ART package in Stata 9 assuming a 3 year recruitment period followed by 1 year of follow up (based on a 2-sided log rank test). The 2 year overall survival rate in patients treated with CRT is approximately 35%. In order to detect an improvement in 2 year overall survival from 35% to 47.5% (Hazard Ratio [HR] =0.71) with 80% power at a 5% significance level a total of 420 patients (269 events) are required. A total of 210 patients will be recruited to each arm.

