### 1.2 Abstract and summary of trial design

SCOPE 1 is a two arm, open, randomised Phase II/III trial. Eligible patients will have histologically confirmed carcinoma of the oesophagus (squamous cell, adenocarcinoma, or undifferentiated carcinoma) and have been chosen to receive definitive chemoradiotherapy (CRT) by an accredited multidisciplinary team (MDT) including a specialist Upper GI surgeon. 420 patients will be randomised to receive definitive CRT with or without cetuximab using a 1:1 ratio (210 patients per arm).

During the first stage (Stage 1) of the study, the trial will assess toxicity (unexpected and expected), activity and feasibility in 90 patients in the experimental arm. Activity will be measured as treatment failure-free rate and feasibility as the number of protocol dose modifications and delays. If toxicity, activity and feasibility are found to be unacceptable recruitment into the trial will stop. If the experimental arm is found to be active, safe and feasible, by the Independent Data Monitoring Committee (IDMC), recruitment will continue into the second stage (Stage 2) of the study. Stage 2 of the study will recruit a further 120 patients into each arm (a total of 420 patients) and compare the overall survival of both groups. The experimental arm of chemo-radiation and cetuximab will be compared against the control arm of chemo-radiation alone. This second stage of the trial is powered to detect a survival advantage with the addition of cetuximab.

All patients randomised into Stage 1 will contribute to the Stage 2 comparison of overall survival. In addition to overall survival, Stage 2 of the study will also assess toxicity, quality of life (QoL) and health economics.

Detailed radiotherapy treatment protocols have been notably absent in recent UK Upper GI Cancer trials involving chemo-radiation, as have procedures to assess adherence to

treatment recommendations. Therefore a detailed radiotherapy protocol and quality assurance procedure will be incorporated in this trial.

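### Stage 1: recruiting 90 per arm does not leave 83 assessable after the stated 10% loss (it leaves 81), and exact power is 86% to 88% rather than 90%

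*Protocol*

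**What the plan says.** Protocol section 12.3 (Stage 1) takes a failure-free rate of about 60% at 24 weeks as the rate with chemoradiotherapy alone. It explains the lower design rate in words: "a treatment failure-free rate of less than 60% would not be sufficiently large enough to warrant further investigation in a Phase III setting". The upper design rate is explained in the second half of that sentence: "but that a rate of 75% or higher would warrant further investigation". The next sentence uses the same values as p1 = 0.60 and p2 = 0.75: "Using a Fleming's single stage design", with alpha 0.05 "and 90% power 83 patients would be required". Whether alpha is one- or two-sided is not stated for Stage 1. The allowance for losses is worded "To allow for 10% not being assessable". The recruitment figure that goes with it is given as "with a 1:1 allocation 90 patients will be recruited into each arm, a total of 180 patients". The section prints no number of failure-free patients at which the arm passes. The IDMC reviews the failure-free rate, toxicity and feasibility before endorsing Stage 2.

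Protocol section 1.2 gives the decision in words. The stop sentence reads "If toxicity, activity and feasibility are found to be unacceptable recruitment into the trial will stop". The sentence after it lets recruitment continue if the IDMC finds the arm active, safe and feasible.

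**The concern.** The allowance and the recruitment figure are stated together and contradict each other, so a later analysis plan cannot reconcile them. If the planned 10% loss occurs, the Stage 1 activity test runs on two patients fewer than the design requires. The stated 90% is also a normal-approximation figure for a test on a count. Its exact power is lower even at 83.

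At stake is the chance of passing a research arm whose true rate is 75%. Stage 1 decides whether the remaining 240 patients are randomised, so its power should be stated correctly.

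Two points of clarity go with this. A reader of section 12.3 sees 60% and 75% but not the pass mark that lies between them. Both sentences in section 1.2 join the three criteria with 'and', so a result in which only some of them are unacceptable is given no decision.

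**Working it through.** **Inputs** (Protocol section 12.3, Stage 1): p1 = 0.60, p2 = 0.75, alpha = 0.05, power 90%, 83 assessable, 10% not assessable, 90 recruited per arm.

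**Step 1: reproduce 83.** The normal-approximation formula for a single-stage, single-arm design is

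n = [(z(1−alpha) × √(p1(1−p1)) + z(power) × √(p2(1−p2))) / (p2 − p1)]²

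- One-sided 5%: [(1.645 × √0.24 + 1.2816 × √0.1875) / 0.15]² = 82.3, so 83. This matches.
- Two-sided 5%: 102.02, so 103. This does not match.

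The design is therefore one-sided, although the protocol does not say so.

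**Step 2: the allowance.**

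- Assessable after 10% loss from 90: 90 × 0.9 = 81, two short of 83.
- Recruits needed for 83 after 10% loss: 83 / 0.9 = 92.2, so 93.
- The cruder inflation, 83 × 1.1 = 91.3, gives 92, which is also not 90.
- Loss that 90 can absorb: (90 − 83) / 90 = 7/90 = 7.8%.

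**Step 3: exact operating characteristics.** For each n, take the smallest count r with P(X ≥ r | n, 0.60) ≤ 0.05. Power is then P(X ≥ r | n, 0.75), with X binomial.

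| Assessable n | Pass mark | Observed rate | Exact alpha | Exact power |
|---|---|---|---|---|
| 81 | ≥57 | 70.4% | 3.5% | 86.2% |
| 83 | ≥58 | 69.9% | 4.1% | 88.4% |
| 90 (all recruited) | ≥63 | 70.0% | 3.2% | 88.7% |

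One success fewer would break 5%: ≥56/81 gives alpha 5.7% and power 90.9%; ≥57/83 gives 6.5% and 92.5%; ≥62/90 gives 5.2% and 92.5%.

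In a search upwards from n = 60, the first size with exact alpha at most 5% and exact power of at least 90% is 85, with a pass mark of 59 (alpha 4.7%, power 90.4%). Allowing for 10% loss, that needs 85 / 0.9 = 94.4, so 95 recruits.

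**Step 4: the same loss on the protocol's own scale.** Normal-approximation power is Φ[(0.15 × √n − 1.645 × √0.24) / √0.1875]. This is 90.2% at n = 83 and 89.6% at n = 81.

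**Step 5: separate the two effects.** Moving from the approximation to the exact calculation at 83 costs 90.2 − 88.4 = 1.8 points. Losing two patients costs a further 88.4 − 86.2 = 2.2 points exact, or 0.6 points by the approximation.

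**Step 6: the denominator.** Section 12.3 sizes on assessable patients, while section 12.5 says all analyses include all randomised patients. The pass mark differs (58 of 83, or 63 of 90), so it should be tied to the denominator used.

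**The case against.** The strongest reply is that this is a two-patient slip. By the method the protocol used, power moves from 90.2% to 89.6%, and exact figures at these sizes jump with the discreteness of the count. A pass mark and its denominator are commonly left to the analysis plan, which section 12.5 promises, and section 18 refers to an IDMC charter; neither is shown. All of that stands. It limits the size of the point but does not make 90 × 0.9 equal 83.

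Three stronger readings are tempting, and the documents do not support them.

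- *60% and 75% as limits on the observed rate.* With n = 83, passing at 60% or above (≥50) would give a 53.0% chance of passing an arm whose true rate is 60%. Passing at 75% or above (≥63) would give 48.3% power. The protocol contains neither rule. It names these values as p1 and p2, which is the ordinary way to motivate a null and a target rate.
- *The stated 5% fails.* It does not. At each design pass mark above, exact alpha is 3.2% to 4.1%.
- *An active but unsafe arm would carry on because the stop sentence needs all three criteria to fail.* Such an arm still fails the written condition for continuing in section 1.2, which section 2.5 repeats. Sections 12.3 and 12.4 require IDMC endorsement, and section 18 gives the decision to the TSC. The stop sentence is loosely worded, and that has no bearing on the 5% or the 90%.

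**Conclusion.** The point holds as an arithmetic inconsistency of modest size. Ninety recruits with 10% loss give 81 assessable patients, not 83; the figure consistent with the stated allowance is 93, and the allowance consistent with 90 is 7.8%. With type I error held at 5%, exact power is 88.4% at 83 and 86.2% at 81, against the stated 90%. Type I error is intact. Stage 2, which is sized separately on overall survival, is untouched.

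This assumes a one-sided alpha, inferred because only that reproduces 83, and a pass mark set as the smallest count that keeps exact alpha at or below 5%. The missing pass mark and the wording of section 1.2 are requests for clarity and do not show that the Stage 1 decision is unsound.

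**What to change.** In section 12.3, do one of the following:

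- keep 90 per arm and restate the allowance as 7 of 90, about 8%; or
- keep the 10% allowance and restate Stage 1 power as about 86% to 88% exact.

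In either case, say that the Stage 1 alpha is one-sided and whether the quoted power is exact or approximate.

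Secondary clarifications:

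- Give the pass mark for the denominator actually used: at least 57 of 81, 58 of 83 or 63 of 90. Give the rule for other denominators too: the smallest count with exact alpha at most 5%.
- Say that 60% and 75% are the design's hypotheses and not limits on the observed rate.
- Reconcile the stop and continue sentences in section 1.2 so that a mixed result has a stated route, leaving the decision with the IDMC and TSC.

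The cost is a few sentences and a slightly less favourable stated allowance or power. No extra patients are needed. Keeping both the 10% allowance and 83 assessable would instead take 93 per arm, three more in each.
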